## Methods

### Study design

This trial was designed based on our previous pilot study [11]. It will be a single-center, randomized, double-blind, placebo-controlled clinical trial with a 24-week intervention and a 36th week follow-up examination. It has been initiated at the Kyung Hee University Hospital at Gangdong, Seoul, Korea, in December 2021 and will be continued till May 2025. A flowchart of this trial is shown in Fig. 1. The schedules for enrollment, interventions, and assessments are presented in Table 1.

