### Assessment

#### K-MMSE and SNSB

K-MMSE will be performed at the screening visit and at 12th week for evaluating the general cognitive status. It is one of the most widely used screening tests to estimate the cognitive functioning [12]. SNSB-II will be conducted at baseline, 24th week, and 36th week, to measure the effect of KGT on cognitive function. Changes in the mean SNSB scores will be analyzed as a primary outcome. SNSB is a neuropsychological test battery most commonly used in South Korea to estimate global cognitive function. The test is composed of various cognitive subtests that assess five domains: memory, attention, language, visuospatial function, and executive function. It also includes other related tests including CDR, K-MMSE, Korean-Instrumental Activities of Daily Living (K-IADL), Barthel-Activities of Daily Living (BADL), and Short-form Geriatric Depression Scale (SGDS) [13]. We will use a modified version of SNSB for dementia (SNSB-D), to obtain a global cognitive function (GCF) score, which is the sum of all the test scores of five domains. The maximum GCF score is 300 points: 150/300 (50%) for memory, 17/300 (6%) for attention, 27/300 (9%) for language, 36/300 (12%) for visuospatial function, and 70/300 (23%) for frontal/executive function [14]. The detailed contents of SNSB-D are presented in Table 3.

**Table 3 Tab3:** Contents of Seoul Neuropsychological Battery for dementia (SNSB-D)

Domains (total score)	Subtests	Maximum points
Attention (17)	Digit span forward	9
	Digit span backward	8
Language & related function (27)	K-BNT	15
	Calculation	12
Visuospatial function (36)	RCFT copy	36
Memory (150)	Orientation	6
	SVLT free/delayed recall	48
	SVLT recognition	12
	RCFT free/delayed recall	72
	RCFT recognition	12
Frontal/Executive function (70)	Motor impersistence	3
	Contrasting program	3
	Go-no-go test	3
	Fist-edge-palm	3
	Luria loop	3
	Categoric word generation	20
	Phonemic word generation	15
	Stroop test-color reading	20
GCF score		300

*K-BNT* Korean short version of the Boston Naming Test, *RCFT* Rey Complex Figure Test, *SVLT* Seoul Verbal Learning Test, *GCF* Global cognitive function

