### Statistics

#### Sample size calculation

The primary outcome of interest in this study is the change in the total SNSB-D score between baseline and post-intervention. The calculation of sample size is based on a superiority test, as the aim of this study is to show that KGT is superior to placebo. Our pilot study of aMCI patients treated with KGT showed that the change in the total SNSB-D score was + 22.47, compared to + 8.36 in the placebo group. The calculated effect size (Cohen’s d) was 0.70. Using G*Power software with a power of 0.80 and a two-sided type I error of 0.05, the calculated total sample size for the current study involves 66 participants, with 33 in each group. The dropout rate was 10% (3 of 33 participants) in the previous study; however, since the current study will take a longer follow-up period, we expect the dropout rate to be 20%. We plan to recruit a total of 84 participants for this RCT (42 participants in each group).

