#### Data analyses

An independent professional statistician, who will also be blinded to the allocation, will perform data analyses using SPSS 20.0 software (IBM, Armonk, NY, USA). Efficacy analyses will be performed using the modified intention-to-treat (mITT) and per-protocol (PP) principles. The mITT population will include participants who have completed at least one examination since the beginning of the intervention. The PP population will include participants who will adhere to the trial protocol and undergo all examinations. Missing data will be adjusted using the last-observation-carried-forward (LOCF) imputation method. A safety test will be performed using the ITT principle. The ITT population will include any participants who will take at least one pack of drugs after randomization. To analyze the efficacy outcome and continuous demographic variables, we will perform the Shapiro-Wilk test to confirm the normality of the data distribution. To analyze the fMRI measures and plasma amyloid beta levels, the paired *t*-test will be used for intra-group comparisons and an independent *t*-test will be used for intergroup comparisons, for normally distributed data. Wilcoxon’s signed rank test will be used for intra-group comparisons and the Mann-Whitney U test for intergroup comparisons of non-normally distributed data. To analyze the scores of the neuropsychological test battery, repeated measures of analysis of variance will be used for parametric data, and the Friedman test for non-parametric data. Categorical demographic variables, conversion to normal cognition or dementia, conversion to positive plasma Aβ42/Aβ40 ratio (< 0.1218), and the incidence of AEs between the groups will be analyzed using the Pearson’s chi-square (χ^2^) test or Fisher’s exact test. Continuous demographic variables will be analyzed using the *t*-test or Wilcoxon signed-rank test. All statistical analyses will be two-tailed, and the significance level will be set at *p* < 0.05.

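### The per-protocol rule demands every examination, so it drops adherent participants with a valid week-24 SNSB-D from one of two unranked efficacy analyses; a minor point, cheap to fix

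*Protocol article*

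**What the plan says.** In the protocol article, Data analyses: "Efficacy analyses will be performed using the modified intention-to-treat (mITT) and per-protocol (PP) principles". The two sets appear side by side. No order is given, and the same two-sided 0.05 level applies to all tests.

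The sets are defined as follows.
- PP: "The PP population will include participants who will adhere to the trial protocol and undergo all examinations".
- mITT: "The mITT population will include participants who have completed at least one examination since the beginning of the intervention".
- Gaps: "Missing data will be adjusted using the last-observation-carried-forward (LOCF) imputation method".

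The outcome used for sizing is in Sample size calculation: "The primary outcome of interest in this study is the change in the total SNSB-D score between baseline and post-intervention". The abstract places the post-intervention visit at week 24. Study design describes a trial "with a 24-week intervention and a 36th week follow-up examination", so week 36 counts as an examination in the article's own terms. Under K-MMSE and SNSB, "SNSB-II will be conducted at baseline, 24th week, and 36th week". The same section schedules a K-MMSE at week 12; the MRI and Blood testing sections schedule scans and plasma amyloid at baseline and week 24.

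**The concern.** A PP set should hold the participants in whom the treatment comparison for a given endpoint was made as planned. This rule ties membership to the whole visit schedule instead. Someone who takes the study drug as required and completes the week-24 SNSB is removed from the PP analysis of the week-24 change if the week-36 visit is missed 12 weeks after treatment ends. Read literally, a missed week-12 K-MMSE, week-24 scan or blood draw has the same effect, although none of these enters the SNSB-D change.

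Two things are at stake. Attendance at week 36 may be related to how the participant fared, so the rule can select on something that happens after the week-24 outcome. And because PP stands level with mITT in a trial that the article calls confirmatory, a PP result shaped by this rule could be presented as the finding.

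**Working it through.** **Inputs from the article (Sample size calculation):** d = 0.70; power 0.80; two-sided alpha 0.05; 1:1 allocation; 33 per arm evaluable; 20% dropout; 42 per arm recruited. On the dropout figure: "since the current study will take a longer follow-up period, we expect the dropout rate to be 20" (per cent). The pilot rate is given as 10% (3 of 33).

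**Reproducing the plan's figures.** The normal approximation gives n per arm = 2 × (1.960 + 0.842)² / 0.70² = 32.04, so 33 per arm and 66 in total. Inflating, 33 / 0.80 = 41.25, so 42 per arm and 84 in total. Both stated figures reproduce. With the noncentral t distribution, 33 per arm gives power 0.7997 and 34 gives 0.812, a negligible difference.

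**Power of the PP comparison at week 24.** Noncentral t with 2n − 2 degrees of freedom and noncentrality 0.70 × √(n/2). The article gives no split of losses between weeks 24 and 36, so the week-24 loss is an assumption and is shown as a range. Total loss by week 36 is held at the stated 20%.

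PP as written: 42 × 0.80 = 33.6 per arm, power 0.807.

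| Assumed loss by week 24 | Per arm if PP needs only the week-24 SNSB | Power | Outcomes regained, both arms |
|---|---|---|---|
| 10% | 42 × 0.90 = 37.8 | 0.852 | 2 × (37.8 − 33.6) = 8.4 |
| 15% | 42 × 0.85 = 35.7 | 0.831 | 2 × (35.7 − 33.6) = 4.2 |
| 20% | 42 × 0.80 = 33.6 | 0.807 | 0 |

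The 20% is a dropout rate and does not count people who stay in the trial but miss a scan or a blood draw. If such gaps raised the share with an incomplete schedule to 25% or 30% (again an assumption), PP as written would keep 31.5 or 29.4 per arm, with power 0.781 or 0.751.

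**Type I error if either set could carry the claim.** For nested sets the correlation of the two test statistics is about √(n_PP / n_mITT). The either-set error is 1 − P(|Z₁| < 1.96 and |Z₂| < 1.96) under a bivariate normal with that correlation.

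| n_PP / n_mITT | Correlation | Either-set error |
|---|---|---|
| 0.95 | 0.975 | 0.060 |
| 0.90 | 0.949 | 0.065 |
| 0.80 | 0.894 | 0.071 |

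A ratio of 0.80 corresponds to 33.6 of 42 per arm, with every randomised participant in mITT. Since mITT requires one examination after the start of treatment, the ratio at 20% loss would be 0.80 or higher and the error about 0.07 or lower.

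**The case against.** The strongest objection is that week 36 is not clearly outside the primary outcome. The abstract lists SNSB change across baseline, week 24 and week 36, the K-MMSE and SNSB section treats the battery at all three visits as primary, and Data analyses plans a repeated-measures analysis of variance or a Friedman test, which use complete visit series. On that reading, a PP rule that asks for the week-36 SNSB matches the planned test. This stands in part. It does not explain why a missed scan, blood draw or week-12 K-MMSE should remove a participant, and it does not fit the week-24 change on which the trial was sized.

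Second, requiring adherence and complete assessments is an ordinary PP definition, and 33.6 per arm is about what the trial was sized for. Both are true, so the power cost is modest.

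Third, ranking analysis sets is commonly left to a statistical analysis plan, which is not at hand. The missing ranking is therefore not a fault in itself. It matters because it gives weight to a PP rule that the article does state.

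A reader might go further in two ways that the article does not support. One is that the trial loses primary data already collected: it does not, since anyone with an examination after the start of treatment stays in mITT, with LOCF for missing visits. The other is that the plan inflates the type I error to about 0.08: no rule says that success on either set suffices, and an error of about 0.078 would need a correlation of 0.8, that is, PP at about 0.8² = 64% of mITT, well below what 20% dropout implies.

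**Conclusion.** The point holds as a minor one. The PP rule as stated is badly matched to the week-24 SNSB-D change, because it makes membership depend on a later visit and on unrelated tests, and the article puts PP level with mITT.

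The effect is confined to PP. With 20% total loss and 10 to 20% lost by week 24 (assumed), a rule tied to the endpoint regains about 8 outcomes of 84 at best and none at worst, with PP power of 0.807 to 0.852 against 0.807. The either-set error of about 0.06 to 0.07 is conditional on a success rule that the article does not contain. Selection on attendance after the endpoint is the better reason to change the rule; its size and direction cannot be judged from the article. The stated sample size is not in dispute.

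**What to change.** Before unblinding, amend the wording in three places.

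1. Name one primary analysis set for the week-24 SNSB-D comparison, either all randomised participants or mITT as now defined, and call PP supportive. The two candidates are not the same: mITT leaves out anyone without an examination after the start of treatment, so the choice should be explicit.
2. Define PP per endpoint: adherence plus the week-24 SNSB for the week-24 change, and the week-36 SNSB only for analyses that use week 36. MRI and blood tests should be required only for the endpoints they supply.
3. Do not narrow mITT to participants with a post-baseline SNSB. The current entry rule is the more inclusive one, and narrowing it would add selection after randomisation to the main analysis.

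The cost is protocol and analysis-plan wording, with no extra participants or data. The drawback is that PP sets will differ in size between endpoints, so each table must state its own numbers. This is a cheap improvement of minor severity.

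### With the SNSB given only at baseline, week 24 and week 36, LOCF scores anyone who leaves before week 24 but stays in the mITT as exactly zero change, which biases the primary contrast

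*Protocol article*

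**What the plan says.** All references are to the Protocol article.

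- Endpoint (Sample size calculation): "The primary outcome of interest in this study is the change in the total SNSB-D score between baseline and post-intervention".
- Schedule (K-MMSE and SNSB): "SNSB-II will be conducted at baseline, 24th week, and 36th week". In between, "K-MMSE will be performed at the screening visit and at 12th week". The Safety assessment section adds blood chemistry at week 12 and vital signs at each visit. No full battery is planned between baseline and week 24.
- Population (Data analyses): "The mITT population will include participants who have completed at least one examination since the beginning of the intervention". Which examination counts is not stated.
- Missing data (Data analyses): "Missing data will be adjusted using the last-observation-carried-forward (LOCF) imputation method". No other method is named. The neuropsychological scores go into a repeated-measures analysis of variance, or a Friedman test if they are not normally distributed.
- Dropout (Sample size calculation): the 24-week pilot lost 3 of 33. Because follow-up is now longer, "we expect the dropout rate to be 20" per cent. No split before and after week 24 is given.

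**The concern.** LOCF can only carry forward what was measured. Someone who attends week 12 has had a K-MMSE and a blood test, so satisfies the mITT condition on its plain reading, but has no SNSB-D after baseline. If that person then leaves, the baseline total is copied to week 24 and the change is zero by construction. The value is then analysed as if it had been observed.

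On the protocol's own planning figures both arms improve, and KGT improves more. Zero therefore understates both arms, and KGT by the larger amount. Dropout may also be related to outcome: the Drop-out criteria include severe adverse events, low compliance, added cognitive medication and loss of the ability to communicate. A participant who worsens and is withdrawn before week 24 is recorded as stable.

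The same rule acts at week 36. A participant seen at week 24 but not afterwards has an on-treatment score carried to a visit 12 weeks after the last dose, which is the visit added to study longer-term effects.

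What is at stake is that the estimated effect of KGT depends partly on how many people leave each arm and when. The sample size takes a different view of the same people: it removes dropouts, whereas the analysis may retain them as zeros.

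**Working it through.** **Inputs.** From Sample size calculation: mean changes 22.47 and 8.36, d = 0.70, power 0.80, two-sided alpha 0.05, 33 evaluable and 42 recruited per arm. Derived: difference 22.47 − 8.36 = 14.11, and SD of change 14.11 / 0.70 = 20.16 (not stated; taken as equal in both arms). All fractions of zeros and all splits between arms below are assumptions.

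**The plan's own figure.** The normal approximation with d = 0.70 gives 33 per arm, 66 in total. The noncentral t gives power 0.7997 at 33 per arm. Inflation: 33 / 0.80 = 41.25, rounded up to 42 per arm, 84 in total. The stated figures reproduce. With no dropout, 42 per arm would give power 0.887.

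**Effect of zeros.** If a fraction q of an arm with mean change m is set to zero, and dropout is unrelated to outcome:

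- arm mean = (1−q) × m
- arm variance = (1−q) × 20.16² + q(1−q) × m²

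The contrast is then tested with a two-sample t-test on week-24 change, 42 per arm.

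**Equal q in both arms.** Difference = (1−q) × 14.11.

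- q = 10%: difference 12.70, pooled SD 19.79, d = 0.642, power 0.828
- q = 15%: difference 11.99, pooled SD 19.54, d = 0.614, power 0.794
- q = 20%: difference 11.29, pooled SD 19.26, d = 0.586, power 0.756 (0.779 in a simulation with exactly 8 zeros per arm)

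**Unequal q.**

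- 30% KGT / 10% placebo: 0.7 × 22.47 − 0.9 × 8.36 = 15.73 − 7.52 = 8.2; power about 0.48
- 10% KGT / 30% placebo: 0.9 × 22.47 − 0.7 × 8.36 = 20.22 − 5.85 = 14.4; power about 0.93

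**No drug effect.** Both arms are given the placebo change, +8.36.

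- Equal q: difference 0, type I error 0.05
- 25/15 split: spurious difference 0.10 × 8.36 = 0.8, type I error about 0.055
- 30/10 split: spurious difference 0.20 × 8.36 = 1.7 against the arm with more dropouts, type I error about 0.07

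**If the mITT excludes some early leavers.** Suppose the whole 20% leave before week 24.

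- All excluded: 42 × 0.8 = 33.6 per arm, no zeros, power 0.807
- Half excluded, half set to zero: 37.8 per arm, 11.1% zeros, power 0.778

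**The case against.** The strongest reply is that the mITT wording limits the damage. Anyone who leaves before a first post-baseline examination is excluded, not imputed. If examination means the SNSB, nobody who leaves before week 24 is zero-imputed at week 24. This stands to that extent: a reader might infer that every early dropout becomes a zero, and the text does not say so. But the text does not restrict the term to the SNSB either, and the week-12 assessments are examinations on its plain reading. Under the narrow reading the week-36 carry-forward remains.

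Second, a reader might infer that power necessarily falls below 0.80. The documents do not support that. The 20% covers the trial to week 36 and was raised because of the longer follow-up; the only 24-week figure is 3 of 33. At about 10% zeros, power is 0.83, because 42 and not 33 per arm are analysed.

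Third, a reader might set both arms at the midpoint of the pilot means, about +15.4, and report for the 30/10 split a spurious difference of 3.1 points and about 11% type I error. That null credits placebo patients with half of the pilot difference. The protocol's own value for an inactive treatment is +8.36, which gives 1.7 points and about 7%.

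Fourth, the 30/10 split is not in the protocol, which reports high adherence in the pilot. That is correct; the split is illustrative, and its mirror image inflates the estimate. The figures are also for a two-sample comparison of week-24 change, not for the planned repeated-measures analysis.

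Finally, the per-protocol analysis requires all examinations and so contains no such zeros. It is restricted to adherent completers, however, and does not address missing data.

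**Conclusion.** The point holds in this form: LOCF on this visit schedule is baseline carried forward for every participant who leaves before week 24 but is kept in the mITT, and it carries an on-treatment score to an off-treatment visit at week 36. Given the protocol's own expected changes, equal zero-imputation reduces the contrast in proportion to q, by 1.4 points at 10% and 2.8 points at 20%. Unequal dropout can move it in either direction, and can create a difference where there is none.

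The loss of power is conditional. With all 42 per arm analysed it drops below 0.80 only when about 15% or more of each arm is zero-imputed. If some early leavers are excluded and others set to zero, it can do so at a smaller share of zeros, but the case computed for this puts the whole 20% before week 24. Under equal dropout with no drug effect there is no bias.

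These sizes rest on an SD derived from d, a common SD, dropout unrelated to outcome, and a simple two-group comparison at week 24. The mechanism itself rests only on the stated schedule, the stated imputation rule and the open wording of the mITT. In a trial presented as confirmatory, that is enough reason to change the rule before unblinding.

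**What to change.** Replace LOCF with a likelihood-based mixed model for repeated measures, or multiple imputation, using all observed SNSB-D scores, and estimate the week-24 difference under missing at random. Add one reference-based or delta-adjusted sensitivity analysis. Replace the undefined examination condition with all randomised participants who have a baseline SNSB-D.

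This changes analysis wording only; no visit or participant is added. The price is reliance on missing at random, which the sensitivity analysis is there to test. Participants with only a baseline score add little information on change, so the gain is mainly less bias. Taking the new analysis as roughly equivalent to a completer analysis, power would be 0.85 against 0.83 at 10% early dropout (37.8 per arm) and 0.81 against 0.76 at 20% (33.6 per arm), a gain of about 2 to 5 percentage points.

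### The sample size is for a two-group test of the week-24 SNSB-D change, but the analysis named is a repeated-measures ANOVA with no effect or contrast specified

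*Protocol article*

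**What the plan says.** Under Sample size calculation, the protocol article fixes the quantity of interest: "The primary outcome of interest in this study is the change in the total SNSB-D score between baseline and post-intervention". It adds that "The calculation of sample size is based on a superiority test". The inputs come from the pilot trial: "the change in the total SNSB-D score was + 22.47, compared to + 8.36 in the placebo group". The article then states: "The calculated effect size (Cohen’s d) was 0.70". The error rates are given as "Using G*Power software with a power of 0.80 and a two-sided type I error of 0.05", and the result is that "the calculated total sample size for the current study involves 66 participants, with 33 in each group". With 20% dropout this becomes 84 recruited, 42 per arm.

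Under Data analyses, the plan for the same scores is: "To analyze the scores of the neuropsychological test battery, repeated measures of analysis of variance will be used for parametric data", with a Friedman test if the data are not normal. The section does not list the visits in the model, say whether the group effect or the group-by-time effect is the test, or name a week-24 contrast. The independent t-test, which would match the sample size, is assigned there to the fMRI and plasma amyloid measures.

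Under K-MMSE and SNSB, the battery is scheduled at baseline, week 24 and week 36. The abstract lists all three time points in its description of the primary outcome.

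**The concern.** A repeated-measures ANOVA over three visits offers two tests that involve treatment, and neither is the week-24 difference in change.

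- The group main effect compares arms on the average of all visits. That average includes the baseline, where randomisation makes the expected difference zero, so the treatment effect is diluted.
- The group-by-time test asks whether the arms' profiles differ in any way over the three visits. It has 2 degrees of freedom and includes week 36, which is 12 weeks after treatment ends. It can be significant without a week-24 effect, and it spends a degree of freedom on a question the sample size did not ask.

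The stated 80% power therefore does not belong to the stated analysis. Neither F-test yields a week-24 treatment difference with a confidence interval, which a trial offered as confirmatory needs. With the effect unnamed, the choice between main effect, interaction and a later contrast also stays open.

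**Working it through.** **Reproducing the plan's figure.** Inputs from Sample size calculation: difference 22.47 − 8.36 = 14.11; d = 0.70, so the implied SD of change is 14.11/0.70 = 20.16; two-sided alpha 0.05; power 0.80. For a two-sample t-test with n = 33 per arm, the noncentrality is 0.70 × √(33/2) = 2.84 on 64 df, and the power is 0.7997. This is 0.80 to rounding, so 33 per arm reproduces. Dropout: 33/0.80 = 41.25, rounded up to 42, or 84 in total. No number of visits, correlation or interaction term is needed to reach these figures. They are those of a two-group comparison of change.

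**Assumptions for the repeated-measures tests** (none is in the article): three visits; compound symmetry with between-visit correlation ρ from 0.5 to 0.9; a fraction f of the week-24 effect remaining at week 36, with f = 1, 0.5 or 0. Set the SD at each visit to 1. The SD of change is then √(2(1−ρ)), and holding d at 0.70 gives a week-24 difference δ = 0.70√(2(1−ρ)). The between-arm differences at the three visits are m = (0, δ, fδ).

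**Group-by-time, 2 and 128 df.** Noncentrality λ = (n/2) × Σ(m − m̄)²/(1−ρ), where the sum is (2/3)(1 − f + f²)δ². Since δ² = 0.98(1−ρ), ρ cancels.
- f = 1 or f = 0: λ = 16.5 × (2/3) × 0.98 = 10.78, power 0.84.
- f = 0.5: λ = 16.5 × 0.5 × 0.98 = 8.085, power 0.71. The term 1 − f + f² is smallest at f = 0.5, so this is the least favourable value between 0 and 1.
- A week-36 difference of size δ with none at week 24, m = (0, 0, δ), also gives λ = 10.78 and power 0.84.
- With an unstructured multivariate test (2 and 63 df), λ cannot fall below 16.5 × 0.49 = 8.085, so power is at least about 0.70.

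**Group main effect, 1 and 64 df.** λ = (n/2) × [δ(1+f)/3]² / [(1+2ρ)/3]. With f = 1, λ = 5.39 at ρ = 0.5 (δ = 0.70) and 0.77 at ρ = 0.9 (δ = 0.313).

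**Week-24 ANCOVA on baseline, 63 df.** The residual variance is (1+ρ)/2 of the change-score variance, so the effective d is 0.70/√((1+ρ)/2). This is 0.808 at ρ = 0.5 and 0.718 at ρ = 0.9.

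Power at 33 per arm:

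| Test | f = 1 | f = 0.5 | f = 0 |
|---|---|---|---|
| Two-group t-test, week-24 change | 0.80 | 0.80 | 0.80 |
| Group-by-time | 0.84 | 0.71 | 0.84 |
| Group main effect, ρ 0.5 to 0.9 | 0.63 to 0.14 | 0.40 to 0.10 | 0.21 to 0.07 |
| Week-24 ANCOVA, ρ 0.5 to 0.9 | 0.90 to 0.82 | 0.90 to 0.82 | 0.90 to 0.82 |

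A simulation of 4,000 trials at ρ = 0.8 agreed: for f = 1, 0.5 and 0, group-by-time gave 0.84, 0.72 and 0.84, and the main effect gave 0.25, 0.16 and 0.11.

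**The case against.** The best defence is that the outcome is defined as change throughout, and the repeated-measures term that compares change between arms is group-by-time. On that reading the power loss is at most about 9 points, and with full or no persistence there is a gain of about 4. This stands. A reader might infer that the trial has far less power than claimed, but that holds only for the group main effect, which the article never names as the test.

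A second defence is that Data analyses does not list the visits. If the model held only baseline and week 24, the group-by-time F would be the square of the change-score t, and there would be no mismatch. That is possible, but nothing in the text restricts the model to two visits, and the abstract and the SNSB schedule point to three. The three-visit model remains an inference.

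Third, the abstract includes week 36 in the primary outcome, so an analysis spanning it is not foreign to the trial. True, but the sample size section then singles out the post-intervention change, and that is what was powered.

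Fourth, the choice of effect, contrast and covariates may be left to an analysis plan that is not shown. Silence on those details alone would be no finding. Here, however, the article names an analysis, and it is not the test it sized.

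Fifth, analysing change without baseline adjustment is valid in a randomised trial. This also stands: adjustment is an improvement, not the correction of an error. A reader might add that the baseline score was used to select low scorers. The inclusion criteria require objective decline on the SNSB but give no cut-off for the SNSB-D total, so that argument is not used.

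**Conclusion.** The mismatch is real. The article powers a two-group comparison of the week-24 change in SNSB-D total and assigns those scores to a repeated-measures ANOVA with no effect or contrast named. Under the likelier group-by-time reading, the main fault is that the test does not isolate week 24; its power is about 0.71 to 0.84 against the planned 0.80. Under a group main effect the loss would be severe: 0.63 to 0.14 with full persistence, and lower with less.

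All the repeated-measures figures rest on assumed compound symmetry, correlation 0.5 to 0.9 and the persistence levels shown. The documents do not support saying that the sample size is wrong or that the trial is grossly underpowered: 66 and 84 are correct for the test they were computed for.

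**What to change.** State one primary analysis: the KGT-minus-placebo difference in SNSB-D total at week 24, adjusted for baseline SNSB-D, from an ANCOVA or from the week-24 contrast of a mixed model. Report it with a 95% CI and one two-sided 5% test. Report week 36 as secondary.

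The 66 evaluable and 84 recruited then stand, with power of about 0.82 to 0.90 under the assumptions above. If the sponsor prefers a repeated-measures effect as primary, it should name that effect and the visits included, and recompute the sample size with stated correlation and persistence assumptions. At 80% power, group-by-time would need 31 to 41 evaluable per arm; the main effect would need 50 (ρ = 0.5) to 338 (ρ = 0.9) even with full persistence.

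The recommended change costs only wording in the analysis section or the analysis plan, with no added patients, visits or measurements. It should be made before unblinding. Baseline adjustment of the MRI and amyloid comparisons is an optional extra and not part of this point.

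### The Friedman test named as the non-parametric analysis of the primary outcome has no treatment-group term, so if that branch is entered it cannot test KGT against placebo

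*Protocol article*

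**What the plan says.** All references are to the Protocol article.

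- **Aim and outcome** (Sample size calculation): "The primary outcome of interest in this study is the change in the total SNSB-D score between baseline and post-intervention", and "the aim of this study is to show that KGT is superior to placebo".
- **Visits** (Assessment, K-MMSE and SNSB): the battery is given at baseline, week 24 and week 36, so each participant has three repeated scores.
- **Normality check** (Data analyses): for the efficacy outcome and the continuous demographics, "we will perform the Shapiro-Wilk test to confirm the normality of the data distribution".
- **Tests for fMRI and plasma amyloid** (Data analyses): paired and independent t-tests, with signed-rank within groups and Mann-Whitney between groups when the data are not normal.
- **Tests for the battery** (Data analyses): in a separate sentence, "repeated measures of analysis of variance will be used for parametric data, and the Friedman test for non-parametric data".
- **Continuous demographics** (Data analyses): t-test "or Wilcoxon signed-rank test".

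**The concern.** The trial asks whether KGT improves the SNSB-D total more than placebo does. A test of that question must contain the treatment group, as a main effect on change or as a group-by-time interaction. Friedman is a one-sample, within-participant rank test. It asks whether scores differ across visits and does not use arm membership.

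This matters because improvement over time without treatment is plausible here. In the pilot, "the change in the total SNSB-D score was + 22.47, compared to + 8.36 in the placebo group", so the placebo arm also gained. A shared gain can make Friedman significant when KGT adds nothing, and a real difference between arms can leave it non-significant. If the data led the statistician into this branch, the pre-specified primary test would say nothing about superiority. Any between-group test then substituted would be a post-hoc choice in a trial that describes itself as confirmatory.

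**Working it through.** **1. The plan's sample size is for a two-group comparison.** Inputs (Sample size calculation): "The calculated effect size (Cohen’s d) was 0.70"; "Using G*Power software with a power of 0.80 and a two-sided type I error of 0.05".
- n per arm = 2(1.960 + 0.842)² / 0.70² = 2 × 7.851 / 0.49 = 32.04, rounded up to 33; total 66, as stated. An exact t calculation gives power 0.7997 at 33 per arm.
- Dropout: 33 / (1 − 0.20) = 41.25, rounded up to 42 per arm; total 84, as stated.

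The number is therefore sized on a between-group difference in change. That sizing is not in question here.

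**2. What Friedman tests.** Each participant's three scores are ranked 1 to 3, the ranks are summed by visit, and the visit sums are compared. Arm appears nowhere in the statistic. This follows from the definition of the test and needs no simulation.

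**3. Illustration of the consequence.**
- From the document: pilot difference 22.47 − 8.36 = 14.11; implied SD of change 14.11 / 0.70 = 20.16; 33 per arm.
- Assumed, not in the document: week-36 mean gain equal to week 24; normal errors; equal variances and a correlation of 0.8 between visits. Under equal variances and correlations, the two changes from baseline correlate at (1 − 0.8) / [2(1 − 0.8)] = 0.5.

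Share of simulated trials with p < 0.05:

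| True mean change (KGT, placebo) | Friedman, arms pooled | Mann-Whitney on week-24 change |
|---|---|---|
| +8.36, +8.36 (no treatment effect) | 82–83% | 5–6% |
| +22.47, +8.36 (planned effect) | 100% | 77% |
| +7.055, −7.055 (same 14.11-point difference) | 4% | about 78% |

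The Friedman rate follows the average change over both arms. The second and third rows have the same treatment difference and give opposite results.

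With skewed (shifted-exponential) errors, the first-row Friedman rate is 28% and the third-row rate 43%; Mann-Whitney gives 5% and 96%. The Friedman rates move greatly with error shape, but under neither shape do they measure the treatment difference.

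**4. How often the branch would be entered if the data were truly normal.** This depends on what Shapiro-Wilk is applied to at the 5% level, which the document does not state.
- One test on the pooled week-24 change: about 5%.
- One test per arm on that change: 1 − 0.95² = 0.0975, about 10%.
- Six arm-by-visit cells, with any rejection counting: about 23–26% in simulation (1 − 0.95⁶ = 0.265 if the cells were independent).

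The distribution of SNSB-D change is not given, so the real rate is unknown.

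**5. Is a between-group rank test assigned elsewhere?** Mann-Whitney completes the scheme opened for the fMRI and amyloid measures. The battery then receives its own pair of parametric and non-parametric tests. No between-group rank test is given to the battery.

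**The case against.** The defect is conditional. Repeated-measures ANOVA is named first and, with a group factor, tests KGT against placebo. A reader might infer that the trial has no valid test of its hypothesis; the document does not support that, because the problem arises only if normality is rejected. This objection stands and limits the point.

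The simulated rates also invite readings that the text does not support:
- **82–83% as a false-positive rate for KGT.** It is a rejection rate for the hypothesis of no change over visits. It becomes an error about treatment only if someone reads a time effect as a treatment effect, which the protocol does not say will be done. It also rests on normal errors, although the branch is meant for non-normal data.
- **By-arm misuse.** Running Friedman separately in each arm would give significance in exactly one arm in about 50% of no-effect trials. No by-arm rule is stated, and that figure includes placebo-only results; KGT-only is about 24%.
- **An easily triggered branch.** The 26% figure needs a six-cell rule that the document does not contain.

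It can also be said that an unseen analysis plan may supply a between-group test. But this is not a detail left open. The protocol names a specific test that does not fit its aim, and a plan with a different test would contradict it.

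Finally, signed-rank for demographics is probably a slip for rank-sum, since the same paragraph pairs signed-rank with within-group and Mann-Whitney with between-group comparisons. It affects no efficacy conclusion.

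**Conclusion.** The point holds in conditional form: if the normality check sends the primary outcome to the Friedman test, the pre-specified analysis contains no comparison of KGT with placebo. This follows from what the test is and from how Data analyses assigns tests, and it does not depend on any simulated rate.

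The rates show the size of the mismatch under stated assumptions: about 82–83% significant with equal gains and no treatment effect, and about 4% with a 14.11-point difference placed symmetrically around zero. The chance of entering the branch with truly normal data lies between about 5% and 26%, depending on an unstated choice. The ANOVA branch and the sample size are not affected. The point should be corrected because it concerns the validity of the primary test in a confirmatory trial.

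The signed-rank test for demographics is a separate and minor error if, as seems intended, the arms are being compared.

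**What to change.** - Remove Friedman as an efficacy test for the neuropsychological scores.
- Pre-specify one between-group test of week-24 change in total SNSB-D, used irrespective of the Shapiro-Wilk result: for example baseline-adjusted ANCOVA, or the group-by-time contrast from the repeated-measures model.
- Name Mann-Whitney on change, or rank ANCOVA, as the sensitivity analysis.
- If the normality switch is kept, the minimum correction is to replace Friedman with Mann-Whitney on week-24 change and to state which data the normality test is applied to.
- Separately, replace signed-rank with the rank-sum (Mann-Whitney) test for continuous demographics compared between arms.

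The cost is a change of wording before unblinding, with no new data or visits. If Mann-Whitney became the primary fallback, its efficiency of 3/π under normality would require 33 / 0.955 = 34.6, or 35 evaluable per arm. That is above the planned 33 but within the 42 recruited; at 33 per arm its simulated power is 0.77 against the planned 0.80.
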